### ***8.3. Requirements for reports, procedures for registration and reporting AEs, and filling out AE Report Forms***

#### ***8.3.1. Documenting and Reporting AEs/SAEs***

At every visit, a record must be made whether or not any AEs occurred during the period from the previous visit. Any adverse event reported for a patient since he/she signed the ICF must be recorded in source documents and in an Adverse Event Report Form (in the CRF). AEs will be documented in accordance with the Sponsor's Manual.

AEs should be registered and numbered consecutively as they occur. Each AE is reported in an *AE Report Form*. Rules for reporting AE/SAE are described in details in the Sponsor's Manual.

Adverse events must be recorded regardless of their seriousness and causal relationship with the study therapy. If an adverse event re-emerges, it must be recorded as a new AE and assigned a new number.

#### ***Laboratory and vital sign abnormalities***

Laboratory and/or vital sign abnormalities considered to be adverse events (assessed as clinically meaningful, including those of CTCAE 4.03 grade 1, inducing clinical symptoms or complaints requiring concomitant therapy or changes in study therapy) must be recorded in the CRF, *Adverse Events* section. All adverse events of CTCAE 4.03 grade 2 or higher must be registered regardless of their clinical significance. It is preferable to specify a diagnosis rather than individual symptoms (for example, anemia instead of decreased hemoglobin). Laboratory abnormalities meeting the criteria for an adverse event should be followed up until they return to normal or until an adequate explanation is obtained.

#### ***8.3.2. AE/SAE reporting***

The AE Report Form should be filled out during the study visit (or the investigator can do it later the same day), except for data not available/not known at that moment. All sections of the form must be filled out. If certain data are not available, the following should be entered: "Data not available" or "N/A". However, all actions should be taken to receive all necessary data on emerging adverse events.

The following information is recorded in source documents and the AE Report Form of the CRF:

- AE No. as it occurred
- Visit No.
- A brief description of the AE

- Seriousness (yes/no)
- Seriousness criterion
- CTCAE 4.03 grade
- Onset date
- Date of resolution (return to normal or baseline)
- Outcome
- Actions taken due to the AE
- Causal relationship with the drug (test drug or reference drug)
- Comments specifying any clinically relevant (in the investigator's opinion) information related to AE development or therapy.

If a medication therapy is administered, its components should be described in section "Concomitant therapy" of the CRF, with a notice that a medication was used to manage the AE.

Columns *Grade*, *Outcome*, *Measures*, and *Causal Relationship* should be filled using digital codes explained in the *Notes* section. If the investigator considers an AE to be an SAE, he/she must fill out an SAE Report Form in addition to an AE Report Form (printed copies).

One SAE Report Form is filled out for one SAE. If the AE remains unresolved at the next visit, the checkbox in the *Adverse Events* section of the eCRF should be ticked for this visit and marked as "unresolved". In this case, a new SAE Report Form should be filled out marked as "Follow-up".

The SAE Report Form must contain the following information:

1. Study information:
  - Protocol ID
2. SAE information:
  - SAE name
  - Initial or Follow-up
  - Internal SAE code assigned by the Sponsor (this field is filled out by the Sponsor)
3. Information on the investigator who reported the SAE, and information on the study site:
  - Full name of the investigator who reported the SAE
  - Contact information (tel. and e-mail)
  - Site name and code
  - Principal Investigator's name
4. Information on the study subject:
  - Patient ID
  - Sex
  - Body weight

- Height
- Date of birth
- Renal/hepatic impairment
- Pregnancy (yes / no)
- Allergies

5. Information on the study drug:

- INN and trade name (if this is a blind study, names are listed with “/”)
- Indication
- Date when the investigational product was first administered
- Number of therapy cycles received (if applicable)
- Drug batch (after which the SAE developed)
- Dose (with which the SAE occurred)
- Treatment start date and time (followed by the SAE)
- Treatment stop date and time (followed by the SAE)
- Route of administration
- Dosage and dosing frequency
- Is the therapy code disclosed or not (for blind studies)

6. Information about recent (within one month) concomitant therapy or that used at the time of SAE onset;

- INNs and brand names of concomitant medications
- Indication
- Treatment start date
- Treatment stop date
- Dosages, frequency and route of administration
- Any suspected causal relationship between the SAE and concomitant medications

7. SAE narrative:

- SAE description with all symptoms and laboratory/instrumental abnormalities and time frames indicated.
- Time after the last dose of the investigational product
- Autopsy data if the subject died (specifying the cause of death according to postmortem conclusion). If no autopsy findings are available, the cause of death should be specified according to the clinical conclusion.

- Time of hospitalization (if applicable)
- 8. Severity (CTCAE 4.03)
- 9. Seriousness
- 10. Medical history (with dates)
- 11. Investigations of particular interest at the onset of the SAE
  - Investigation
  - Normal limits
  - Date of the analysis
  - Result
- 12. Actions taken to resolve the SAE
  - Medication / non-medication
  - For medication therapy the following should be specified: INNs and brand names of drugs, treatment start and stop dates, dosages, frequencies and routes of administration.
- 13. Actions taken regarding the investigational product
  - Discontinued/ dose reduce / unchanged
  - Dechallenge/rechallenge test results (if applicable)
- 14. Outcome
- 15. Signatures

The investigator **must** sign (put a signature and a full name) each page of the SAE Report Form to verify his/her responsibility for the reported information. Signed SAE Report Form is then submitted to the Sponsor.

#### ***8.4. Methods and duration of follow-up for study subjects after the onset of AE/SAE***

If the patient is withdrawn from the study due to an AE/SAE, the investigator should perform further patient's treatment and follow-up as per standard institutional practices for the treatment of the certain AE or SAE. The patient should be followed up until **the AE/SAE resolves completely**. In case of any laboratory, instrumental or vital sign abnormality, the patient should be followed up until the abnormality resolves completely (in other words, until the abnormality resolves or improves to the baseline level).

See section 5.4 for further details.

**The patient withdrawn from the study due to pregnancy** that occurred during the study should be monitored through the entire pregnancy and for 6 months after delivery to evaluate the mother's and child's health. Information on pregnancy course and outcome should be recorded in the source documentation. During the entire period of pregnancy, the investigator in collaboration with

the attending Ob/Gyn specialist should monitor the patient's overall health, the course of pregnancy, and laboratory values including ultrasound. When the child is born, the investigator together with the attending pediatrician should monitor the newborn for 6 months evaluating the child's clinical status and the laboratory/instrumental findings.

**If the study subject's partner becomes pregnant**, the study subject should provide the contacts of attending Ob/Gyn specialist to the investigator. The investigator should monitor woman's health over the entire course of pregnancy. Monitoring should be performed via phone calls to attending Ob/Gyn specialist once every 3 months to analyze the overall woman's health, pregnancy course, and laboratory and instrumental findings including the ultrasound findings. When the child is born, the investigator together with the attending pediatrician should monitor the newborn for 6 months evaluating the child's clinical status and the laboratory/instrumental findings.

#### **8.5. Immunogenicity study**

Immunogenicity of BCD-057/Humira® will be assessed using the proportions of patients who develop antibodies to adalimumab (binding and/or neutralizing).

The immunogenicity analysis will include all patients who received at least one dose of BCD-057/Humira®. Patients whose serum samples taken on Day 1 of Week 0 and at least one serum sample taken on any subsequent visit (weeks 16, 33, and 55) are missing/lost/spoiled, will be removed from immunogenicity analysis.

Immunogenicity of BCD-057/Humira will be assessed by evaluating titers of binding and neutralizing anti-adalimumab antibodies (BAbs and NABs).

## 9. Statistics

### 9.1. Description of statistical methods

#### *Quantitative data*

The quantitative data in this study include the following:

#### *Efficacy:*

- PASI
- BSA
- sPGA
- NAPSI
- Itch severity (VAS, 0 mm to 100 mm).
- Health-related quality of life (DLQI and SF-36)

#### *Safety:*

CBC results

- Biochemistry results
- Urinalysis results
- Vital signs (BP, pulse, body temperature)

#### *Pharmacokinetics:*

- Adalimumab concentration in the serum

The statistical analysis will be performed using two-tailed hypothesis tests. The statistical significance level is 0.05.

The Shapiro-Wilk test will be used to test the qualitative data for normality.

Normally distributed data will be compared using the following tests: the two-tailed Student's *t*-test, Welch's *t*-test, and ANOVA.

Non-normally distributed data will be compared using the following tests: the Mann-Whitney test, Wilcoxon test, Kruskal-Wallis test, and Friedman's test.

To describe the normally distributed quantitative variables, the following parameters will be used: means, SDs, min, max, and coefficient of variation. For non-normally distributed quantitative data, it is planned to use median and quartiles, minimum, maximum, and coefficient of variance.

The statistical hypothesis of the equivalence by the primary endpoint will be tested by comparing limits of the 95% CI with the equivalence margin.

The null hypothesis ( $H_0: |\varepsilon| \geq \delta$ , where  $\delta$  is the equivalence margin) is rejected, and the drugs are considered equivalent if the bounds of the 95% CI for the difference in the mean proportions of PASI 75 responders fall within the equivalence margin ( $\delta = 0.15$ ).

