#### ***1.4.3. Conclusions***

Comparative physicochemical and non-clinical studies as well as the Phase I study of the PK, tolerability, and safety in healthy volunteers did not show any statistically significant differences between BCD-057 and Humira®. Thus, it is expected that, in this study in patients with moderate-to-severe plaque psoriasis, BCD-057 will demonstrate the efficacy, safety, immunogenicity, and PK similar to those of the originator.

The risks of adverse events have been thoroughly investigated. The treatment with adalimumab very rarely results in severe or life-threatening reactions and is expected to have low immunogenicity. At the same time, multiple international clinical studies of TNF $\alpha$  blockers and the wide clinical experience gained with Humira® suggest the benefit for the patients participating in the study. In

adalimumab clinical studies, a PASI 75 response was achieved by 80% patients, a reduction in sPGA to score 0 or 1 was achieved by up to 70%, the BSA decreased, and the patients' quality of life improved. Thus, the total risk/benefit ratio for subjects participating in this clinical study is considered favorable.

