This study is to compare the pharmacokinetics of BCD-057 and Humira® in a limited patient population (90 subjects from each study arm, 180 subjects total). This investigation is necessary to demonstrate that pharmacokinetics of these drugs is similar not only in healthy volunteers but in psoriasis patients as well (who may differ from healthy subjects in terms of adalimumab PK). In patients with plaque psoriasis, adalimumab is used for a long time, so it is important to study its PK parameters at steady state – when an equilibrium between the intake of the drug and its elimination has been achieved. Adalimumab fully exerts its clinical effects when reaches the steady state concentration. In addition, steady-state PK allows predicting how rapidly the serum levels of the active ingredient decrease is the patient misses a dose or discontinues the drug.

It is known that the time to steady state equals 3 to 5 half-life periods of adalimumab. For adalimumab, the average half-life is 2 weeks, varying from 10 to 20 days [8]. Thus, the maximum time to steady state will be 100 days or 14.3 weeks ( $20 \times 5 = 100$ ). According to literature data, adalimumab concentrations reach the steady state in 12 to 16 weeks. Blood specimens will be

---

 Adalimumab M04-688 Pharmacokinetic Report

[http://www.abbvie.com/assets/research/clinical-trials-data-and-information-sharing/synopses/adalimumab\\_M04-688.pdf](http://www.abbvie.com/assets/research/clinical-trials-data-and-information-sharing/synopses/adalimumab_M04-688.pdf)

taken at frequent intervals after the 9th injection of adalimumab (at weeks 15 and 16), and thus the PK of BCD-057/Humira® will be studied at steady state.

In the second period of the study, some patients will be crossed over from one drug product to another. After completing Week 24 and all appropriate assessments, one half of patients from the Humira® arm will be switched to BCD-057. The rest of patients who were originally randomized to receive Humira® will continue the treatment with Humira®.

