#### ***PK endpoints***

(PK population includes only 90 subjects from each arm, 180 subjects total)

- $AUC_{tau,ss}$  after multiple SC injections of Humira® / BCD-057.
- $C_{av,ss}$ ,  $C_{max,ss}$ ,  $C_{min,ss}$ ,  $C_{trough}$  after multiple SC injections of Humira® / BCD-057.

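### In the readable text, section 9.1 puts PK under two-tailed tests of difference, which cannot demonstrate the similar PK that section 1.5.1 asks of the PK sub-study

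*Protocol*

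**What the plan says.** Section 1.5.1 gives the reason for sampling 90 patients per arm: "This investigation is necessary to demonstrate that pharmacokinetics of these drugs is similar not only in healthy volunteers but in psoriasis patients as well". The PK endpoints in section 4.1.2 are AUCtau,ss, Cav,ss, Cmax,ss, Cmin,ss and Ctrough, with the note "PK population includes only 90 subjects from each arm, 180 subjects total".

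Section 9.1 lists the quantitative data under efficacy, safety and pharmacokinetics. Its only PK entry is "Adalimumab concentration in the serum". The text then continues, for quantitative data generally: "The statistical analysis will be performed using two-tailed hypothesis tests. The statistical significance level is 0.05". The methods follow: "Normally distributed data will be compared using the following tests: the two-tailed Student's *t*-test, Welch's *t*-test, and ANOVA". Rank tests (Mann-Whitney, Wilcoxon, Kruskal-Wallis, Friedman) are named for data that are not normal. The one equivalence procedure in the section is tied to efficacy: "The statistical hypothesis of the equivalence by the primary endpoint will be tested by comparing limits of the 95% CI with the equivalence margin". Its margin, 0.15, applies to the difference in PASI 75 proportions.

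Section 3 states a hypothesis for PASI 75 only. The end of section 9.1 lets methods be chosen once the data are in, and lets the list be extended.

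**The concern.** A claim of similarity needs an interval estimate held against limits fixed beforehand. The tests named for PK take no difference as the null hypothesis. A non-significant result may only mean that the data are noisy, and a significant one may reflect a difference too small to matter. Section 9.1 uses the right kind of rule for PASI 75 and, in the readable text, does not extend it to PK. It also names concentration, whereas the endpoints to be compared are AUCtau,ss and the other steady-state parameters.

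Supplementary report No. 1 will present the PK results with the 33-week data. If section 9.1 were followed as it reads, that report would carry p-values for difference and no criterion by which the aim in section 1.5.1 could be met or missed.

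**Working it through.** **Passages side by side**

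| Place in the protocol | Content on PK |
|---|---|
| 1.5.1 | Aim: demonstrate similar PK in patients |
| 2.1, 2.2 | Milder wording: study and determine steady-state PK parameters |
| 3 | No PK hypothesis |
| 4.1.2 | Five PK parameters, no acceptance range |
| 9.1 | Concentration among data compared by two-tailed 0.05 tests; interval rule for PASI 75 only |
| 9.3 | Readable only in its opening, under an efficacy sub-heading; the rest is redacted |
| 9.8 | PK population, no criterion |

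**The plan's own figure.** The sub-study size of 90 per arm cannot be reproduced. No PK variability, expected ratio, acceptance range or PK power is readable.

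**Illustration of size.** From the documents: n = 90 per arm, two-sided 5% test. Assumed: analysis of log AUC by t-test, between-subject CV of 30% to 80%, and for comparison a 90% CI for the ratio lying inside 0.80-1.25. All 90 per arm are taken as evaluable.

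Formulas:
- SD of log AUC: s = sqrt(ln(1 + CV²)).
- Standard error of the log ratio: SE = s × sqrt(2/90).
- Noncentrality: ln(true ratio)/SE, with 178 degrees of freedom and critical value 1.973.

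Worked values:
- CV 50%, ratio 0.80: s = 0.472, SE = 0.0704, noncentrality = -0.2231/0.0704 = -3.17, P(non-significant) = 0.117.
- CV 80%, ratio 0.80: s = 0.703, SE = 0.1048, noncentrality = -0.2231/0.1048 = -2.13, P(non-significant) = 0.438.
- CV 30%, ratio 0.90: s = 0.294, SE = 0.0438, noncentrality = -0.1054/0.0438 = -2.41, P(significant) = 0.668.

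The interval rule was evaluated by simulation.

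| CV | Ratio 0.80: test non-significant | Ratio 0.80: CI rule accepts | Ratio 0.90: test significant | Ratio 0.90: CI rule accepts | Ratio 1.00: CI rule accepts |
|---|---|---|---|---|---|
| 30% | 0.1% | 5% | 67% | 85% | 99.9% |
| 40% | 3% | 5% | 45% | 65% | 97% |
| 50% | 12% | 5% | 32% | 51% | 87% |
| 60% | 23% | 5% | 24% | 40% | 70% |
| 70% | 35% | 5% | 20% | 31% | 53% |
| 80% | 44% | 4-5% | 17% | 23% | 37% |

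At CV 30% and a true ratio of 0.90, the same trial gives a significant difference and an interval inside 0.80-1.25 in 52% of cases. That overlap falls to 10% at CV 40% and to none from CV 50%. The two kinds of error therefore belong to different ranges of variability: a small difference flagged at low CV, a 20% deficit missed at high CV.

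**The case against.** The strongest objection is the redaction. Most of section 9.3 is blacked out, and a section that opens with an efficacy sub-heading may go on to PK, especially as 90 per arm is derived nowhere else. A reader might infer that the difference tests are the only PK analysis in the plan. The documents do not support that; it can be said only of the readable text.

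A reader might also infer that a non-significant PK result would be reported as similarity, and a significant one as failure. No readable sentence says how a PK p-value will be interpreted. Section 1.4.3 does say that earlier studies "did not show any statistically significant differences between BCD-057" and Humira and goes on to expect similar results. But it is a general summary that spans physicochemical, non-clinical and Phase I work, and sections 1.2 and 1.3.2.1 call the Phase I PK equivalent. It does not establish how this sponsor would read a PK test.

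Three further points carry weight. The test list in section 9.1 is generic and assigns no test to AUCtau,ss, so the log-AUC t-test above is a model of the written approach and not a quotation of it. The formal objectives use softer wording than section 1.5.1. Log transformation, interval level and acceptance range are often left to an SAP.

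The last point does not dispose of the matter. Section 9.1 does more than leave detail open: it places PK under a class of test that cannot serve the aim in section 1.5.1. An SAP with an interval criterion would still disagree with that text. The freedom to choose methods after the data are in does not help either, because it fixes no PK criterion in advance.

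**Conclusion.** The point holds as a mismatch between aim and method in the readable protocol. Section 1.5.1 wants similar PK demonstrated; section 9.1 offers PK only tests of difference and reserves the interval rule for PASI 75. If the redacted part of section 9.3 contains a PK criterion, the defect becomes a conflict between 9.1 and 9.3, and 9.1 still needs correcting.

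The size depends on a variability that the documents do not give. With 90 per arm and log AUC, a true ratio of 0.80 would escape detection in about 12% of trials at CV 50% and 44% at CV 80%, but in 3% or less at CV 40% or below. At CV 30% a ratio of 0.90 would be significant in 67%, although the 90% CI rule with an assumed 80-125% range accepts it in 85%. It would be too strong to say that both errors threaten the trial equally, since they arise mainly at different CVs. The primary efficacy analysis is unaffected. The change should be made, and fixed before the 33-week PK analysis.

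**What to change.** In section 9.1, exempt PK from the paragraph on two-tailed difference tests. State that AUCtau,ss is log-transformed and that the BCD-057/Humira geometric mean ratio is estimated with a 90% CI. Similar PK is concluded if that interval lies within a prespecified acceptance range: the one in section 9.3 if it gives one, otherwise for example 80.00-125.00%. Present the other PK parameters as ratios with the same intervals, descriptively. A body-weight covariate is optional. If the sponsor does not want a PK criterion, the consistent alternative is to call the PK comparison descriptive and reword section 1.5.1.

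The cost is one paragraph in section 9.1 and matching text in the SAP, with no extra patients, samples or visits. The downside is that the similarity claim can now fail for imprecision. At a true ratio of 1.0, with 90 evaluable per arm and the 80-125% range, it passes in about 87% of trials at CV 50% and about 70% at CV 60%.

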### ***Categorical data***

The categorical data in this study include the following:

#### ***Efficacy:***

- The proportion of patients with a 75% PASI reduction from baseline.
- The proportion of patients with 50% and 90% PASI reduction from baseline.
- The proportion of patients with sPGA score reduced to 0 (complete clearance) or 1 (minimal disease).

#### ***Safety:***

- ECG findings.
- Urinalysis results.
- The proportion of patients who experienced AEs that, in the investigator's opinion, are related to Humira® or BCD-057.
- The proportion of patients who experienced grade 3/4 AEs (CTCAE v. 4.03) that, in the investigator's opinion, are related to Humira® or BCD-057.
- The proportion of patients in each study arm who experienced AEs potentially due to TNF $\alpha$  inhibitors. These AEs include infections, serious infections, opportunistic infections (infections caused by opportunistic pathogenic viruses or cellular organisms), tuberculosis, malignancies, demyelinating diseases, lupus-like syndrome, congestive heart failure, allergic reactions, injection site reactions, and CBC or blood biochemistry abnormalities.
- The proportion of patients who discontinued the study due to AEs/SAEs, by study arms.

